#### Training Component

Training is a strategic component of the project and is designed as an integrated educational intervention with theoretical, practical, and supervised components. Its purpose is to improve recognition of suspected maltreatment, appropriate documentation, awareness of legal and ethical responsibilities, confidence in multidisciplinary communication, and correct use of the REDCap registry.

The theoretical phase will include in-person lectures and e-learning modules. Training content will cover definitions and typologies of maltreatment, clinical warning signs, differential diagnoses, trauma-informed communication with children and families, documentation standards, legal and institutional reporting pathways, interprofessional coordination, data protection, and correct use of the digital registry.

The practical phase will include online and interactive webinars; hands-on sessions on data entry into the registry; and small-group supervision sessions led by experts in pediatrics, psychology, and forensic medicine. The effectiveness of the training will be evaluated using a pretest-posttest repeated-measure design. Each participant will complete a knowledge and competency assessment questionnaire before and after the training. The questionnaire will include multiple-choice questions and clinical scenarios aimed at measuring participants’ ability to recognize indicators of abuse, activate appropriate reporting pathways, and use the digital tool effectively.

Participants’ satisfaction, perceived usefulness, confidence, and perceived transferability to clinical practice will be assessed after training using 5-point Likert-scale items and open-ended questions. Results will be summarized using descriptive statistics and complemented with thematic qualitative analysis of open-ended responses to identify perceived strengths, implementation barriers, training needs, and suggestions for improvement.

Exploratory multivariable analyses will identify predictors of training gain, satisfaction, registry usability, and active registry use considering age, professional role, years of experience, work setting, previous child protection training, and frequency of registry use.

### Outcomes and Measurement Time Points

The primary outcome is registry usability, measured using the mean SUS score collected after participants use the registry. Specifically, the SUS will be administered once at the end of the 12-month registry activation and follow-up period or earlier for participants who discontinue participation after having completed the minimum required registry exposure. Eligible respondents will be trained and authorized hospital or community professionals involved in suspected maltreatment recognition, documentation, or case management. To ensure that SUS responses reflect actual exposure to the tool, participants will be included in the primary SUS analysis only if they have entered at least one registry record or completed at least one supervised registry use session or simulation. Participants without any registry exposure will not contribute to the primary SUS analysis.

Secondary outcomes include feasibility indicators (active users, number of records, completion of mandatory fields, technical support requests, and time to complete a report), training outcomes (pretest-posttest knowledge and competency scores, satisfaction, and qualitative feedback), and reporting outcomes (number and rate of suspected maltreatment reports, reporting timeliness, duplicate reports, follow-up documentation, and activation of child protection pathways). Baseline data will be collected before training and registry activation, posttraining outcomes will be collected immediately after training, and registry usability and implementation outcomes will be collected during registry use and at the end of the observation period.

### Data Management, Confidentiality, and Registry Workflow

Registry data will be entered using predefined forms by trained and authorized professionals. Records will be entered by the professional who identifies or manages the suspected case or by another authorized member of the clinical team directly involved in the case according to local organizational arrangements. Follow-up information will be updated when new nonidentifying information becomes available regarding referral, pathway activation, multidisciplinary evaluation, or case management outcome. Records will be saved under a unique study code and stored on secure institutional servers or approved REDCap infrastructure. The registry will not contain direct identifiers. Data access will be role based and limited to authorized members of the research team. Data exports for analysis will be anonymized, stored in password-protected files, and used only for the objectives approved by the ethics committee. Data quality will be checked periodically by designated members of the research team through REDCap validation rules, completeness checks, audit trails, and review of mandatory fields. Any inconsistencies, missing mandatory information, or potential duplicate records will be resolved using only nonidentifying registry information. Potential duplicate reports will be assessed through predefined nonidentifying linkage variables, including time window, age group, sex, setting, and event characteristics. When a potential duplicate is detected, the research team will retain a single registry record for analysis and update it with additional nonidentifying information when appropriate. Duplicate management will not involve access to direct identifiers and will not interfere with clinical or legal reporting procedures.

Any suspected maltreatment identified in clinical practice will continue to be managed through ordinary institutional and legal reporting pathways; the registry is an evaluation and documentation tool and does not replace mandatory reporting procedures. Mandatory reporting will remain a separate clinical and legal process carried out through existing institutional channels and according to applicable law. Entry of information into the research registry will be separate from the activation of the appropriate clinical and legal pathway and will not be considered a substitute for mandatory reporting. No direct identifiers or legal reporting documents will be uploaded to the registry.

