### Implementation Components and Procedures

#### Registry Component

The digital registry will be developed using the REDCap platform, a system widely used in clinical research for secure data collection, management, and analysis. The registry will be configured with role-based access, audit trails, structured data entry fields, mandatory and optional variables, and data quality checks. Access will be restricted to authorized project personnel, and all data management procedures will comply with applicable institutional policies and data protection regulations.

The registry will collect only anonymized or non–directly identifiable information required for research and service evaluation. Data fields will include child age group and sex, date and setting of contact, type of suspected maltreatment (physical, psychological, or sexual maltreatment; neglect; or exposure to domestic violence), warning signs, risk and protective factors, reporting source, referral or follow-up arrangements, and case management outcome. Each record will be assigned a unique alphanumeric study code. Direct identifiers, such as name, fiscal code, address, telephone number, or full date of birth, will not be entered into the research registry. Potential duplicate reports will be managed through predefined nonidentifying linkage variables, including time window, age group, sex, setting, and event characteristics, without attempting to reidentify the child.

Registry usability will be evaluated using the System Usability Scale (SUS), a validated 10-item questionnaire yielding scores from 0 to 100 [44]. SUS completion will be restricted to trained and authorized professionals with documented exposure to the registry, as detailed in the Outcomes and Measurement Time Points section. Feasibility indicators will include number of active users, number of records created, proportion of completed mandatory fields, average time required to complete a report, number of technical support requests, proportion of records with documented pathway activation, and completeness of follow-up fields. These indicators will allow for evaluation of whether the registry reduces data fragmentation and supports standardized clinical and operational terminology.

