### Registry Phase Results

The registry component will generate implementation results on the use of the REDCap platform for systematic, secure, and standardized recording of suspected child maltreatment reports [45]. Reported results will include the number of trained users, number of active registry users, number of records created, completion of mandatory fields, time required for report completion, and number of technical or workflow issues identified during implementation.

The analysis will describe whether the registry provides a more unified view of suspected cases and care pathways than the preimplementation documentation process. Completeness, traceability, documented actions, follow-up fields, and pathway activation will be used as operational indicators of report quality.

Registry usability will be described using SUS scores, reported as means, SDs, medians, IQRs, 95% CIs, and the proportion of scores below 70 and above 80 [44]. To evaluate implementation, reporting rates will be compared before and after registry introduction and expressed as reports per professional month and, where denominators are available, per 1000 pediatric contacts.

The registry will describe suspected cases by maltreatment type, child characteristics, family and social context, access route, setting, referral pathway, follow-up, and outcome. These data will help assess whether the model can generate useful local information to support prevention strategies, service indicators, and health care planning.

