### Overall Evaluation Outcomes

Integrated statistical analysis of registry and training data will describe the feasibility, usability, acceptability, and preliminary implementation impact of the combined registry training system as a prevention and monitoring model.

Performance indicators will include average reporting time, percentage of fully completed registry forms, proportion of reports with documented follow-up, proportion of cases with activation of child protection pathways, number of duplicate or repeat reports, and rate of active participation of professionals in the platform.

The elaboration of these data will provide a solid foundation for defining regional quality benchmarks in the management of suspected child maltreatment cases, identifying replicable best practices and areas for improvement. Quantitative and qualitative results, interpreted in an integrated manner, will also validate the project’s methodological model, confirming its feasibility and transferability to other regional or national contexts.

From a scientific standpoint, Sentinel will produce preliminary evidence on the feasibility of digital registries in pediatrics and on the contribution of multidisciplinary training to early detection and standardized documentation of suspected child maltreatment. The data collected will be disseminated through reports and peer-reviewed publications, contributing to the international literature on child protection and digital health.

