### Limitations

Despite its innovative potential, the project has several limitations that warrant careful consideration. First, its monocentric and pilot nature limits the generalizability of the findings, which will need confirmation in larger and more diverse settings. Data collection, carried out by a relatively small group of professionals, may be influenced by organizational or individual variables such as workload and familiarity with digital tools.

Another limitation concerns the quality and completeness of registry data. As the registry is designed as a very simple tool, the reliability of the information will depend even more on participants’ consistency and engagement, reinforcing the need for basic but continuous supervision and periodic checks. Similarly, the effectiveness of training may vary according to participants’ motivation and contextual differences between hospital and community settings. Finally, the relatively short project duration precludes comprehensive evaluation of long-term effects, particularly regarding the sustainability of the network and the retention of acquired skills. To consolidate the results, follow-up assessments and ongoing professional development programs will be required.

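### Registry completeness is an outcome, yet missing mandatory fields are checked and resolved during the study, so an end-of-period count would mix user entry with study-driven correction

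*Protocol article*

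**What the plan says.** Completeness appears as an outcome in four places in the protocol article:

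- Registry Component lists the "proportion of completed mandatory fields" among the feasibility indicators, along with completeness of the follow-up fields.
- Outcomes and Measurement Time Points places it among the secondary outcomes: "feasibility indicators (active users, number of records, completion of mandatory fields, technical support requests, and time to complete a report". The primary outcome is the mean System Usability Scale score.
- Registry Phase Results gives it an interpretive role: "Completeness, traceability, documented actions, follow-up fields, and pathway activation will be used as operational indicators of report quality".
- Overall Evaluation Outcomes names the "percentage of fully completed registry forms" as a performance indicator and says the data will help define regional quality benchmarks.

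Data Management, Confidentiality, and Registry Workflow describes what is done to the same records while the study runs. "Data quality will be checked periodically by designated members of the research team", by means that include completeness checks and review of mandatory fields. Then: "Any inconsistencies, missing mandatory information, or potential duplicate records will be resolved using only nonidentifying registry information". For a potential duplicate, "the research team will retain a single registry record for analysis and update it with additional nonidentifying information when appropriate".

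Study Design also plans ongoing monitoring of completeness. On timing, Outcomes and Measurement Time Points says only that implementation outcomes are collected while the registry is in use and at the end of observation. Registry Component and the data-management section both mention audit trails, but neither ties them to the completeness count.

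**The concern.** The indicator is meant to show whether professionals can and do complete the registry. A procedure written into the study acts on that same quantity. Filling blanks can only raise the completion rate, and merging partial duplicates into one updated record pushes the same way. If the count is taken from the records as they stand at the end, part of the figure reflects the study's checking and not the users' entry.

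Two uses of the figure make this matter. Feasibility shares the primary objective with usability (Study Design), and the results are intended to inform regional benchmarks and transfer to other settings, where a research team may not be checking the fields. Registry Phase Results also sets the registry against the documentation process that preceded it, for which no comparable central checking is described.

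The Limitations section says the reliability of the data will depend on participants' consistency and engagement, "reinforcing the need for basic but continuous supervision and periodic checks". A completeness figure taken after resolution partly conceals that dependence.

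**Working it through.** The documents give no expected completion rate, target, resolution rate or number of mandatory fields, so there is no stated figure to reproduce. The check has two parts.

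**1. The provisions side by side**

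- What is counted: completed mandatory fields and fully completed forms.
- What changes it: resolution of missing mandatory information after periodic checks, and updating of merged records.
- When it is counted: during use and at the end. An end-of-period count falls after whatever resolution has taken place. A count during use could fall before or after it.
- Who changes the field: for merged duplicates, the research team. For other missing fields, the sentence is passive and names no one.
- With what information: only what is already in the registry and nonidentifying.

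**2. Size, as an illustration with assumed inputs**

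Let c be the share of mandatory fields complete at first entry and r the share of blanks later resolved. Both are assumptions.

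Reported field completion = c + (1 − c) × r

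| c | r = 0 | r = 0.25 | r = 0.50 | r = 0.75 |
|---|---|---|---|---|
| 0.60 | 0.600 | 0.700 | 0.800 | 0.900 |
| 0.75 | 0.750 | 0.8125 | 0.875 | 0.9375 |
| 0.90 | 0.900 | 0.925 | 0.950 | 0.975 |

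Example: 0.75 + 0.25 × 0.50 = 0.875.

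The part of the reported figure due to resolution is (1 − c) × r divided by the reported value. Over the cells with r above 0 it runs from 0.025/0.925 = 2.7% (c = 0.90, r = 0.25) to 0.30/0.90 = 33% (c = 0.60, r = 0.75). It would exceed the part due to user entry only if (1 − c) × r > c, that is, c < r/(1 + r). Even with every blank resolved (r = 1), that requires c below 0.50.

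The form-level indicator is more sensitive. With k mandatory fields, taken as independent and equally complete (a further assumption):

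Fully completed forms = [c + (1 − c) × r]^k

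With c = 0.95:

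| k | r = 0 | r = 0.25 | r = 0.50 | r = 0.75 |
|---|---|---|---|---|
| 10 | 60% | 68% | 78% | 88% |
| 15 | 46% | 56% | 68% | 83% |
| 20 | 36% | 47% | 60% | 78% |

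Example: for k = 15 and r = 0.50, 0.975^15 = 0.684, against 0.95^15 = 0.463 with no resolution.

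At r = 0 neither indicator is distorted. The rule confining resolution to registry information keeps r down, since a value recorded nowhere in the registry could not be filled under it.

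**The case against.** The strongest defence is that the article does not say completeness is counted after resolution. Collection during use and ongoing monitoring are both compatible with a count taken beforehand, and a counting rule for a descriptive indicator may well sit in a fuller document. The Statistical Analysis section also promises to describe missing data by variable and time point. This stands as far as it goes: the documents do not establish that the figure will be inflated. It does not dispose of the point, because the issue is a stated procedure that alters a stated outcome. The promised description of missing data does not say whether it precedes resolution.

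Other parts of the defence also stand:

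- A reader might infer that research staff fill the blank fields themselves. Outside duplicate merging, the text does not say so. A clinician who completes a field after a reminder is still entering data, although the study prompted it.
- A reader might assume that most blanks will be filled. Nothing supports a high resolution rate, and the restriction to registry information argues against one.
- A reader might conclude that the bias must always favour the registry. Filling blanks can only raise completeness, but the same sentence covers inconsistencies, whose resolution could remove a value, and the net effect may be nil.
- The checks are not shown to be purely a research activity. Data quality checks are configured in the registry, and supervision is part of the training being evaluated.
- Counting everything at first submission would be unfair to follow-up and outcome fields, which may not be knowable then.

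**Conclusion.** The point holds in a limited form. Completeness is a secondary, descriptive indicator, and the plan provides for study-driven correction of the fields it counts. A count at the end of observation would mix the two and could overstate how complete the registry would be in routine use.

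The stronger inference, that the indicator measures the team's cleaning in place of what clinicians entered, is not supported. No passage fixes the count after resolution, and in the illustration resolution outweighs user entry only when fewer than half the fields are complete at entry.

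The size cannot be determined from the documents. Under the assumed ranges, field completion could be raised by 2.5 to 30 percentage points (0.90 to 0.925; 0.60 to 0.90), with larger relative changes possible at form level and none if nothing is resolved.

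No threshold, test or progression rule rests on the figure, and the primary outcome is unaffected. It is still worth changing, because the figure feeds the feasibility conclusion and the proposed benchmarks.

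**What to change.** - Count completion of mandatory fields that can be known at entry, and full completion of the initial form, as they stand at the user's first submission. Take this from the audit trail, before any research-team check, query or duplicate merge.
- Assess follow-up fields separately at the end of follow-up. Split them into entries made without a query and entries made after one, and keep both.
- Report completeness after resolution, with the number of corrections per record, as a separate data-quality figure.
- State who may change a mandatory field after a check.

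The cost is wording in the outcome definitions and an extraction from an audit trail that the registry is already planned to have. No new data or design change is needed. The reported completeness may be less favourable. The Results section says data analysis has not started, so the definition can still be set before results are seen.

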### Study Setting and Timeline

The study will be conducted within the coordinating pediatric hospital and its connected community pediatric network. The 24-month timeline will include approximately 3 months for registry development and internal testing, 3 months for recruitment and baseline assessment, 3 months for training delivery, 12 months for registry activation and follow-up data collection, and 3 months for final analysis and dissemination. Minor adaptations to these periods may be made according to ethics approval timelines and operational feasibility.

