### Statistical Analysis

#### Overview

Quantitative analyses will be performed using recognized statistical software, such as SPSS, R, or Stata. Descriptive statistics will be calculated for all study variables. Continuous variables will be summarized as means and SDs or medians and IQRs according to distribution. Categorical variables will be summarized as frequencies and percentages. All estimates will be reported with 95% CIs when appropriate.

Pretest-posttest comparisons of knowledge and competency scores will be performed using 2-tailed paired-sample *t* tests when normality assumptions are met, as assessed using the Shapiro-Wilk test and visual inspection of distributions. When assumptions are not met, Wilcoxon signed-rank tests will be used. Mean change scores, standardized effect sizes, and 95% CIs will be reported to support interpretation of training effectiveness.

Registry usability will be evaluated by calculating the mean SUS score and comparing it with established interpretive benchmarks, where scores of 70 or higher are considered acceptable and scores of 80 or higher indicate excellent usability [44]. A 1-sample *t* test or Wilcoxon signed-rank test will be used to compare observed SUS scores with the prespecified benchmark depending on distributional characteristics.

Changes in reporting rates of suspected child maltreatment before and after implementation will be analyzed using Poisson regression models, estimating incidence rate ratios with 95% CIs. The primary pretest-posttest comparison will use reports per professional month as the operational denominator. When service volume data are available, additional models will use the number of pediatric consultations or contacts as an offset to estimate reports per 1000 contacts. Overdispersion will be assessed by comparing the deviance and Pearson chi-square statistics with the df; if overdispersion is present, negative binomial regression or robust SEs will be applied. Repeated reports and potential duplicates will be described separately and, in sensitivity analyses, excluded or counted once per suspected case according to the predefined duplicate management rules.

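### Registry records are reduced to one on a merely potential match, so different children may be merged, and the analysis section handles the same records differently

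*Protocol article*

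**What the plan says.** All references are to the protocol article.

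- **Data Management, Confidentiality, and Registry Workflow** fixes the rule: "When a potential duplicate is detected, the research team will retain a single registry record for analysis". The retained record may then be updated with further non-identifying information. The same section limits the evidence that may be used: "potential duplicate records will be resolved using only nonidentifying registry information".
- **Registry Component** names the matching fields as "predefined nonidentifying linkage variables, including time window, age group, sex, setting, and event characteristics". The registry holds "child age group and sex, date and setting of contact, type of suspected maltreatment", and full date of birth is not entered. Exposure to domestic violence is one of the listed types: "type of suspected maltreatment (physical, psychological, or sexual maltreatment; neglect; or exposure to domestic violence".
- **Who enters, and where.** "Records will be entered by the professional who identifies or manages the suspected case or by another authorized member of the clinical team". On the setting: "The study will be conducted within the coordinating pediatric hospital and its connected community pediatric network".
- **Statistical Analysis, Overview** describes a different handling for the reporting-rate models: "Repeated reports and potential duplicates will be described separately and, in sensitivity analyses, excluded or counted once per suspected case", following the predefined duplicate rules.
- **Outcomes and Measurement Time Points** lists number of records, number and rate of reports, and duplicate reports as secondary outcomes. Overall Evaluation Outcomes lists duplicate or repeat reports as a performance indicator.

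**The concern.** The trigger for keeping one record is that a duplicate is *potential*. The text describes no confirmation, and the evidence allowed is registry content only. The matching fields describe a kind of case rather than a particular child. Two sisters in the same age group, brought in together after the same episode of domestic violence, could agree on every named field, and one would drop out of the analysis. Unrelated children with the same profile inside the window could be lost in the same way.

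What is at stake is the count of records, the number and rate of reports, and the count of duplicates. Chance matches rise roughly with the square of the number of records, so the share lost rises with volume. If the rule governs the main analysis, it works against detecting the increase in reporting that the project hopes to show.

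The second problem is that the two sections do not agree on which records enter the main rate analysis.

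**Working it through.** **No figure to reproduce.** The article gives no expected number of records, duplicate rate, window length, age bands or match logic. What follows illustrates the order of magnitude and does not estimate the actual loss.

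**Inputs from the article:** a minimum of 30 professionals (Participants and Recruitment); 12 months of registry activation (Study Setting and Timeline); five maltreatment types (Registry Component).

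**Assumed inputs:** 4 equal age groups, 2 equal sexes, 2 equal settings, types split 25/15/10/25/25%, entry dates uniform over 365 days, every record a different child, agreement required on all fields, and no siblings. Volumes of 36, 72 and 120 records correspond to 0.1, 0.2 and 0.33 reports per professional month (for example 0.1 × 30 × 12 = 36).

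**Formula.** Expected chance-alike pairs = C(N,2) × P(two dates within the window) × the product over fields of Σp².

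- Window of w days: P = 1 − (1 − w/365)². For 30 days this is 0.158; for 7 days it is 0.038.
- Age, sex and setting: 1/4 × 1/2 × 1/2 = 1/16.
- Type: 0.25² + 0.15² + 0.10² + 0.25² + 0.25² = 0.22.

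For 36 records and 30 days: 630 × 0.158 × 1/16 × 0.22 ≈ 1.4 pairs, or 1.4/36 ≈ 3.8% of records. For 7 days: 630 × 0.038 × 1/16 × 0.22 ≈ 0.33 pairs, or 0.9%.

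**Simulation of the collapse rule** (a record is lost if it matches a retained record on all fields within the window), as % of distinct cases lost:

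| Event detail | Window | 36 records | 72 records | 120 records |
|---|---|---|---|---|
| Type only | 7 days | 0.9 | 1.8 | 3.0 |
| Type only | 30 days | 3.7 | 7.1 | 11.3 |
| Type plus one further four-level field | 7 days | 0.2 | 0.5 | 0.8 |
| Type plus one further four-level field | 30 days | 0.9 | 1.9 | 3.1 |

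**A second set of assumptions** (settings 60/40, types 30/15/10/30/15%) gives 4.1%, 9.6% and 17.3% at 36, 90 and 180 records for 30 days. Across windows of 7 to 90 days it runs from 1.0% to 36.0%. Siblings would add to all these figures; finer event detail would reduce them.

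**If agreement on setting is not required**, the second set gives 7.6%, 16.7% and 28.6% for 30 days instead of 4.1%, 9.6% and 17.3%. A looser match is therefore safe only if it raises a flag and does not itself remove a record.

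**The two sections side by side.** Data management keeps one record for analysis once a potential duplicate is detected. The analysis section describes potential duplicates separately and excludes them or counts them once in sensitivity analyses, which implies that the main model still contains them. If the first governs, the main count is already reduced and the sensitivity analysis has little left to remove. If the second governs, the main count is not reduced, but the sensitivity analysis and the duplicate count still rest on unconfirmed matches.

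**The case against.** - **The matching detail may sit in the full protocol.** The linkage variables and rules are called predefined, and an article need not give window, age bands or algorithm. This stands for those details. It does not answer the rule that the article does state: a potential match leads to one retained record.
- **Missed hospital-community duplicates.** A reader might infer that records of one referred child, entered in both places, escape detection because they differ on setting, so that counts are wrong in both directions. The documents do not support this. Setting is listed among variables through which duplicates are assessed, the list is open, and nothing says two records must agree on it. The risk would exist only if agreement were required, and its size cannot be derived: assuming that 20% of children are entered twice merely returns a 20% over-count.
- **The rate counts reports, not children.** The Registry Component section defines the numerator as reports recorded, so two professionals reporting one child is not plainly an over-count. This stands, and it supports counting all reports in the main model.
- **The sizes depend on assumptions.** This stands. One extra event field cuts the loss about fourfold, and the protocol refers to event characteristics in the plural.
- **Reviewers may use audit trails.** Two records entered by one user on one day are informative. The text allows this but does not make it a condition for merging.
- **Restricting resolution to registry data protects privacy.** This stands. Asking two professionals whether they saw the same child would not work without exchanging identity unless a referral links them, so such a query is not proposed.

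**Conclusion.** The point holds in limited form. As written, the data management rule lets a potential match on coarse fields remove a record from analysis, so different children may be merged and counts of records, reports and duplicates may be biased. Under the main set of assumptions the loss is 0.2% to 11.3% of distinct cases; wider windows and higher volumes push it further. It is negligible with a short window and detailed event fields, and material with a window of a month or more and few event fields. The actual value cannot be known from the article.

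Separately, the data management and analysis sections conflict over whether de-duplication belongs to the main analysis or to sensitivity analyses. That conflict needs no assumption.

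The documents support *may be biased*, not a demonstrated error in either direction. The effect is confined to secondary, preliminary reporting outcomes; the primary SUS outcome is untouched. The change is worth making because the affected counts are named outcomes and the data are meant to inform regional benchmarks.

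**What to change.** 1. Treat a match as a flag. Keep every original record, with the flag stored beside it.
2. Do not make agreement on setting a condition for flagging.
3. Add two non-identifying fields: *sibling also recorded*, and *referred from / already recorded by another network service*. The second partly overlaps the existing reporting-source and referral fields and could extend them.
4. Merge only when these fields, or the same entering professional, confirm the same child and the same episode. Otherwise keep both records.
5. Reconcile the two sections: state that the main rate model counts all recorded reports, and give two count-once sensitivity analyses as bounds, one collapsing confirmed duplicates only and one collapsing all flagged pairs.

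**Cost.** Two extra fields and a short check on flagged records, with no identifiers exchanged. Data collection began in April 2026, so any records entered before the fields are added will lack them. Unless the same entering professional can confirm such a pair, it should stay flagged and unmerged.
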